## **Abstract**

### **Background**

Knee osteoarthritis (OA) is a prevalent disabling disorder that involves changes in articular cartilage damage, subchondral bone remodeling, synovitis, and abnormal infrapatellar fat pad (IPFP). Due to the complicated etiology and numerous phenotypes of knee OA, limited improvement is achieved for treatments among knee OA patients with different phenotypes. Inflammatory OA phenotype is a typical knee OA phenotype, and individualized treatment targeting on inflammation is a promising way to obtain an optimal therapeutic effect for people with inflammatory knee OA phenotype. Glucocorticoid is a traditional anti-inflammatory drug for knee OA and intra-articular glucocorticoid injections are recommended clinically. However, emerging evidence has shown the repeated intra-articular glucocorticoid injections for a long term would induce cartilage loss. IPFP and its adjacent synovium are considered as the main source of inflammation in knee OA. This GLITTERS trial aims to investigate if a glucocorticoid injection into the IPFP is effective and safe over 12 weeks among knee OA patients with an inflammatory phenotype.

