Glucocorticoid is a traditional anti-inflammatory drug for knee OA. It suppresses inflammation via the apoptosis induction of immune cells and the suppression of the proinflammatory mediators expression. Clinically, intra-articular glucocorticoid injections are recommended for people with knee OA to reduce their pain. However, emerging evidence has shown that repeated intra-articular injections over two years would induce more cartilage loss. Thus, the injection of glucocorticoid into IPFP may not only play a better role in anti-inflammatory but minimize the cartilage deterioration among inflammatory knee OA patients. To date, there is no study about the injection of drugs into IPFP.

The characteristics of real-time imaging and tracking in ultrasonography make the injection into inflammatory sites of IPFP possible. Therefore, we hypothesized that the IPFP injection of glucocorticoid can effectively reduce the knee pain and effusion-synovitis volume, compared to the placebo injection among people with symptomatic knee OA who have effusion- and Hoffa-synovitis.

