**Table 1. Schedule of data collection**

|                                               | Screening/
Baseline | 4 weeks* | 8 weeks* | 12 weeks |
|-----------------------------------------------|------------------------|----------|----------|----------|
| Primary outcomes                       |                        |          |          |          |
| Knee pain (VAS)                               | ✓                      | ✓        | ✓        | ✓        |
| Effusion-synovitis volume #        | ✓                      |          |          | ✓        |
| Secondary outcomes                     |                        |          |          |          |
| WOMAC                                         | ✓                      | ✓        | ✓        | ✓        |
| Hoffa-synovitis score #
(MOAKS) | ✓                      |          |          | ✓        |
| Quality of life (AQoL-4D)                     | ✓                      | ✓        | ✓        | ✓        |
| Pain medication use                           | ✓                      | ✓        | ✓        | ✓        |
| infrapatellar fat pad volume #     | ✓                      |          |          | ✓        |

|                                                           |   |   |   |   |
|-----------------------------------------------------------|---|---|---|---|
| Adverse reaction                                          |   | ✓ | ✓ | ✓ |
| Other measures                                     |   |   |   |   |
| Demographic data †                             | ✓ |   |   |   |
| Clinical evaluation § and history collection   | ✓ |   |   |   |
| Ultrasonographic examination in the study knee            | ✓ |   |   |   |
| Effusion-synovitis score # (MOAKS)             | ✓ |   |   | ✓ |
| Tibiofemoral bone marrow lesion maximum size # | ✓ |   |   | ✓ |
| Tibiofemoral cartilage defect #                | ✓ |   |   | ✓ |
| Use of medication & supplements                           | ✓ | ✓ | ✓ | ✓ |
| Adverse events                                            |   | ✓ | ✓ | ✓ |
| Depression (PHQ-9)                                        | ✓ | ✓ | ✓ | ✓ |

VAS: visual analogue scale; WOMAC: Western Ontario and McMaster Universities Osteoarthritis Index; MOAKS: MRI Osteoarthritis Knee Score; AQL-4D: four-dimensional Assessment of Quality of Life; PHQ-9: nine-items Patient Health Questionnaire.

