## Questionnaires and queries

The VAS (100 mm visual analog scale) will be used to assess knee pain using the standard question: “On this line, how would you rate your knee pain in the last week?”. A higher score indicates a higher level of pain severity.

The WOMAC requires patients to rate their pain (five items), stiffness (two items), and functional dysfunction (17 items) in the last week. Each item is a 100-mm visual analog scale. The WOMAC score is calculated by summing the score of each

item with every 1 mm representing one point. A higher WOMAC score indicates a more severe OA symptom. When more than five items are not completed, the WOMAC score would be regarded as missing data. Otherwise, the WOMAC score would be calculated by averaging the remaining score and then multiplying by 24.

The AQL-4D will be used to assess the quality of life in the last week. It comprises four dimensions of independent living, social relationships, psychological well-being, and physical senses. Each dimension has three items with four response categories ranging from 0-3. The total AQL-4D score ranges from 0-36, and a higher score indicates a lower quality of life.

The PHQ-9 will be used to assess the depression in the last two weeks. It comprises nine items with four response categories scored from 0-3. The total PHQ-9 score ranges from 0-27, and a higher score indicates a more severe depression level.

Queries about medications and supplement use will also be recorded at baseline and each follow-up. Adverse events and reactions will be recorded at each follow-up. Pain medication use would be determined by the researchers from the records of medication use. Adverse events are defined as any untoward event occurring during the trial, regardless of its relation to treatment, and they need to be reported spontaneously when they occur. Details of the adverse event will be recorded and whether it is an adverse reaction will be determined.

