### **2.2. Objectives**

- Primary aim: to assess whether the injection of glucocorticoid into the IPFP can effectively reduce the knee pain measured by visual analogue scale (VAS) and MRI measured effusion-synovitis volume, compared to the placebo injection among patients with symptomatic knee OA who have both effusion- and Hoffa-synovitis.
- Secondary aims: to evaluate whether the injection of glucocorticoid into the IPFP effectively reduces the total Western Ontario and McMaster Universities Osteoarthritis Index (WOMAC) score, MRI-assessed Hoffa-synovitis score,

and pain medication use; improves the quality of life; and has a difference in IPFP volume and adverse reaction, compared to the placebo injection among symptomatic knee OA patients with both effusion- and Hoffa-synovitis.

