### **6.2. Analysis methods**

Baseline characteristics will be displayed in descriptive statistics according to the data type. Continuous variables with normal distribution will be displayed by means and standards deviation. Continuous variables with non-normal distribution will be displayed by median and interquartile range. Category variables will be displayed by proportion.

The intention-to-treat analysis will be the primary analyses method. The per-protocol analysis will be the second analyses method where the per-protocol population is defined as participants completed four follow-ups without major protocol deviations. There is no interim analysis in this research. Mixed-effects regression models will be used to calculate treatment group differences with continuous measures. In the models, fixed effects will be follow-up time, baseline covariates (including age, sex, BMI, baseline value of the corresponding outcome), treatment, and interactions between follow-up time and baseline covariates and treatment. Study site and individual participant identification will be treated as the random intercepts and follow-up time as the random slop in the models. The overall treatment group differences will be calculated by the linear combination of the estimated coefficients. Wilcoxon rank-sum test will be used to analyse the difference in pain medication use between the treatment and placebo groups. Pain medication use will be classified as commenced/increased, unchanged, or discontinued/decreased. The chi-square test or Fisher's exact test will be used to compare the incidence of adverse reactions between the two treatment groups, and the number of adverse reactions will be reported as the number of participants reporting at least one adverse reaction.

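### Events judged to be adverse reactions are the only events compared between arms; all-cause and serious adverse events have no planned by-arm summary, and no safety comparison has a planned confidence interval

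*Combined protocol and SAP*

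**What the plan says.** **Aim.** The protocol abstract asks whether the injection "is effective and safe over 12 weeks among knee OA patients with an inflammatory phenotype". The operational aim is narrower. SAP 2.2, matching the protocol Objectives, asks whether the injection "has a difference in IPFP volume and adverse reaction" compared with placebo.

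**Collection.** The protocol (Questionnaires and queries) defines adverse events without regard to cause and then adds a filter: "Details of the adverse event will be recorded and whether it is an adverse reaction will be determined". It does not say who makes that judgement or by what criteria. Table 1 lists adverse reactions as a secondary outcome and adverse events under other measures, both at weeks 4, 8 and 12.

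**Analysis.** The protocol Statistical plan and SAP 6.2 name one event analysis: a chi-square or Fisher's exact test "will be used to compare the incidence of adverse reactions between the two treatment groups", counting participants with one or more reactions. SAP 6.1 lists adverse reactions and IPFP volume as outcomes, but not all-cause or serious adverse events. SAP 4.1 has confidence intervals in its title but sets only a P threshold and a multiplicity position.

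**Imaging.** "Tibiofemoral cartilage defect" and bone marrow lesion size are scheduled at baseline and week 12 in Table 1. Neither is in the SAP 6.1 outcome list or named in a method.

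**Context.** The Introduction states: "To date, there is no study about the injection of drugs into IPFP". There is no Data Monitoring Committee (Audits and steering) and no interim analysis (SAP 6.2).

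**The concern.** A test restricted to judged reactions sees only what the person assessing causality recognises as related. At a site that the plan describes as unstudied, an unfamiliar effect is the one most likely to be recorded as unrelated. The all-cause record would show it, but the plan does not commit to tabulating that record by arm. Serious events are mentioned as grounds for emergency unblinding and withdrawal, but no table is planned for them.

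With no monitoring committee and no interim analysis, the final tables are the only place where the plan sets out a by-arm look at events. If those tables hold one P value from 60 participants and no interval, a reader may take non-significance as support for the word safe in the abstract.

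The cartilage and lesion readings raise a smaller issue. They are collected but not named in the analysis, so whether and how they are reported is left open until after the data are seen.

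**Working it through.** **1. What each safety-relevant measure receives**

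| Measure | Collected | In SAP 6.1 | Named method | Interval planned |
|---|---|---|---|---|
| Adverse reactions | weeks 4, 8, 12 | yes | chi-square or Fisher | no |
| IPFP volume | baseline, week 12 | yes | mixed model, as a continuous outcome | not stated |
| Adverse events, any cause | weeks 4, 8, 12 | no | none | no |
| Serious adverse events | within adverse events | no | none | no |
| Cartilage defects, lesion size | baseline, week 12 | no | not named | no |

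**2. The plan's own sample size.** Inputs from SAP 3.3: Z values 1.96 and 0.842, σ = 24.2 mm, δ = 19.9 mm, 20% loss.

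n = 2 × [(1.96 + 0.842) × 24.2/19.9]² = 23.2, rounded up to 24; 24/(1 − 0.20) = 30 per arm.

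The stated figure reproduces. It rests on pain, and nothing in the plan sizes or bounds a safety comparison.

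**3. What a non-significant Fisher test means at this size.** The documents give no event rates, so those below are assumptions. Power is by full enumeration, two-sided 0.05.

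| Assumed rates | 24 per arm | 30 per arm |
|---|---|---|
| 5% vs 15% | 11% | 9% |
| 5% vs 20% | 24% | 24% |
| 5% vs 30% | 56% | 63% |
| 10% vs 30% | 31% | 37% |
| 10% vs 40% | 60% | 70% |

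Against zero events in one arm, significance needs at least 6 of 30 (20%) or 5 of 24 in the other.

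**4. What zero events leaves open.** The two-sided exact 95% upper limit is 1 − 0.025^(1/n): 11.6% for 0/30 and 14.2% for 0/24. The chance that one arm of 30 shows at least one case of an event with true rate 1%, 2% or 5% is 1 − (1 − p)^30 = 26%, 45% or 79%.

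**5. How filtering dilutes a difference.** Let p₁ and p₀ be the proportions with an event caused by the study injections. Suppose that the judgement recognises a share s of these in both arms, with no false attributions. The compared difference is then s(p₁ − p₀). For an assumed 20% and 5%, the true difference is 15 points; with s = 0.5 the test sees 10% − 2.5% = 7.5 points.

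Counting every cause also has a cost. With an independent background rate b in both arms, the difference in participants with any event is (1 − b)(p₁ − p₀); with b = 0.2 that is 0.8 × 15 = 12 points. The all-cause difference is the smaller one when b exceeds 1 − s. The documents give neither s nor b, which is a reason to report both counts.

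**6. Cartilage.** The defect score sums four compartments graded 0 to 4, so it runs from 0 to 16. The difference detectable with 80% power in an unadjusted comparison is 2.802 × √(2/n) standard deviations: 0.72 SD at n = 30 and 0.81 SD at n = 24.

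**The case against.** The strongest reply is that the plan analyses the aim it sets. The Objectives ask about IPFP volume and adverse reactions; both are listed outcomes and both have a method. That stands. A reader might infer that the trial cannot support its safety aim, but the documents do not bear that out for the aim as worded. The gap is against the broader wording of the abstract. Nor are adverse reactions the only safety comparison, because IPFP volume measures the injected tissue. They are the only event-based one.

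Second, researchers and outcome assessors are to be blinded, and the unblinded injectors take no other part, so misattribution should be largely non-differential. That is fair and argues against bias in favour of either arm. It does not remove dilution, and for harm dilution works towards missing it.

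Third, SAP 6.2 applies mixed models to continuous measures in general, with baseline adjustment. A reader might infer that cartilage has no analysis at all; that is not established, since the sentence may be meant to cover the defect sum. It is still a poor specification for that score: with baseline as a covariate there is one reading per participant, so a participant intercept and a time slope cannot be separated from residual error.

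Fourth, a reader might infer that the trial leaves its cartilage rationale unexamined although the data exist. The documents do not support this. The Introduction says that "repeated intra-articular injections over two years would induce more cartilage loss" and expects the IPFP route to "minimize the cartilage deterioration among inflammatory knee OA patients". This trial gives one injection, follows participants for 12 weeks, and has no intra-articular glucocorticoid arm. No analysis of its data could show that the route spares cartilage.

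Last, the 11.6% limit for 0/30 comes from sample size. It would apply equally to all-cause events and does not measure the cost of comparing reactions alone. It bears only on the case for intervals.

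**Conclusion.** The point holds as an inexpensive improvement that should be made. The plan commits to one event-based safety test, on causality-filtered events, with no interval. All-cause and serious adverse events have no by-arm summary, and the cartilage and lesion readings are unnamed in the analysis. The primary analyses are unaffected.

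The size of the dilution cannot be computed, because the documents give neither event rates nor accuracy of attribution; the figures in step 5 are illustrations. The precision argument is firmer. Over the assumed rate pairs, power at 30 per arm runs from 9% to 70%, so a non-significant result would be weak evidence of safety whichever count is tested. The added analyses would not let 60 participants establish safety. They would show which differences are excluded and which are not.

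**What to change.** - **SAP 6.1 and 6.2:** add, by arm, the number of participants with at least one adverse event of any cause and with at least one serious adverse event. Give each a risk difference and exact 95% confidence interval, with the interval method named. Count participants in their randomised arm, including any withdrawn after emergency unblinding.
- **Adverse reactions:** keep the planned comparison alongside, with its own risk difference and interval. State who judges causality, by what criteria, and whether that person is blinded.
- **Conclusion:** limit any safety statement to what the intervals exclude, and say that a non-significant P value will not be read as evidence of safety.
- **Imaging:** name the 12-week change in tibiofemoral cartilage defects and in bone marrow lesion size as descriptive safety measures, each compared by a regression adjusted for its baseline value. Describe them as a weak short-term harm check against placebo and not as a test of whether the route spares cartilage.

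All the data are already scheduled for collection. The cost is SAP text and a few more tables. The downside is more safety comparisons, which should be labelled descriptive.

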### 6.3. Missing data

In our study, we anticipate no missing data for baseline characteristics, including age, sex, BMI, and study site. For the outcomes, we assume that any missing values are missing at random. To address these missing values, we used multiple imputations with chained equations. Imputations were performed independently for each group, based on baseline variables (age, sex, BMI, and study site) and non-missing values at other time points. Additionally, multiple responses were treated as missing.

### 6.4. Statistical software

All analyses will be performed using SAS version 9.4 (SAS Institute, Institute, Carey, North Carolina, USA) or R4.0.3 (The R Foundation of Statistical Computing).

